**6. Possible complications and risks**

None.

**7. Patient information and consent**

Patient Information Sheet and Informed Consent Form are attached. Patients will be notified that they are free to participate and also free to discontinue from the study at any time.

**8. Patient data protection**

The Study Protocols and Informed Consent Form will be stored in a securely locked cabinet, maintaining confidentiality. Patients will be identified by subject number only for the purpose of randomization and encoding the computer database.

# Attachment:

Bibliographic references

Stroop color-word interference test

Standford Sleepiness Scale

Study flow charts

Patients Information Sheet

Informed Consent Form

## Color-word interference test

(J. R. Stroop, 1935)

The Stroop color-word interference test is a useful and reliable assessment tool for the identification of executive function deficits. As the basic principle of Stroop test is competition of semantic meaning and font font color, subjects were shown colored words with conflicting visual and verbal information which led to interference in word and color meanings.

First task – word name

Study participants should read the written color names of the words independently of the color of the ink as fast as possible. The time will be measured by a stop-watch. Mistakes will be marked (X over the words).

Second task – color name

Study participants should name the color of the letters independently of the written word as fast as possible. The time will be measured by a stop-watch. Mistakes will be marked (X over the words).

## Color-word interference test (preoperative)

First task – word name

Please read the written color names of the words independently of the color of the ink as fast as possible. The time will be measured and mistakes will be marked (X over the words).

Name: _________________________ Date: __________ ___________

| **Red** | **Blue** | **Yellow** | **Green** | **Yellow** | **Green** | **Yellow** | **Red** | **Green** | **Red** |
| --- | --- | --- | --- | --- | --- | --- | --- | --- | --- |
| **Blue** | **Green** | **Red** | **Yellow** | **Red** | **Green** | **Green** | **Blue** | **Red** | **Yellow** |
| **Green** | **Blue** | **Red** | **Blue** | **Blue** | **Red** | **Green** | **Blue** | **Green** | **Blue** |
| **Yellow** | **Green** | **Red** | **Green** | **Yellow** | **Red** | **Blue** | **Red** | **Blue** | **Red** |
| **Red** | **Yellow** | **Red** | **Green** | **Green** | **Blue** | **Red** | **Yellow** | **Blue** | **Green** |

**Time: First task ____________ sec Mistakes: First task ___________**

**Investigator: _____________________**

## Color-word interference test (preoperative)

Second task – color name

Please name the color of the letters independently of the written word as fast as possible. The time will be measured and mistakes will be marked (X over the words).

Name: _________________________ Date: __________ ___________

| **Red** | **Blue** | **Yellow** | **Green** | **Yellow** | **Green** | **Yellow** | **Red** | **Green** | **Red** |
| --- | --- | --- | --- | --- | --- | --- | --- | --- | --- |
| **Blue** | **Green** | **Red** | **Yellow** | **Red** | **Green** | **Green** | **Blue** | **Red** | **Yellow** |
| **Green** | **Blue** | **Red** | **Blue** | **Blue** | **Red** | **Green** | **Blue** | **Green** | **Blue** |
| **Yellow** | **Green** | **Red** | **Green** | **Yellow** | **Red** | **Blue** | **Red** | **Blue** | **Red** |
| **Red** | **Yellow** | **Red** | **Green** | **Green** | **Blue** | **Red** | **Yellow** | **Blue** | **Green** |

**Time: Second task ____________ sec Mistakes: Second task ___________**

**Investigator: _____________________**

## Color-word interference test (postoperative)

First task – word name

Please read the written color names of the words independently of the color of the ink as fast as possible. The time will be measured and mistakes will be marked (X over the words).

Name: _________________________ Date: __________ ___________

| **Red** | **Blue** | **Yellow** | **Green** | **Yellow** | **Green** | **Yellow** | **Red** | **Green** | **Red** |
| --- | --- | --- | --- | --- | --- | --- | --- | --- | --- |
| **Blue** | **Green** | **Red** | **Yellow** | **Red** | **Green** | **Green** | **Blue** | **Red** | **Yellow** |
| **Green** | **Blue** | **Red** | **Blue** | **Blue** | **Red** | **Green** | **Blue** | **Green** | **Blue** |
| **Yellow** | **Green** | **Red** | **Green** | **Yellow** | **Red** | **Blue** | **Red** | **Blue** | **Red** |
| **Red** | **Yellow** | **Red** | **Green** | **Green** | **Blue** | **Red** | **Yellow** | **Blue** | **Green** |

**Time: First task ____________ sec Mistakes: First task ___________**

**Investigator: _____________________**

## Color-word interference test (postoperative)

Second task – color name

Please name the color of the letters independently of the written word as fast as possible. The time will be measured and mistakes will be marked (X over the words).

Name: _________________________ Date: __________ ___________

| **Red** | **Blue** | **Yellow** | **Green** | **Yellow** | **Green** | **Yellow** | **Red** | **Green** | **Red** |
| --- | --- | --- | --- | --- | --- | --- | --- | --- | --- |
| **Blue** | **Green** | **Red** | **Yellow** | **Red** | **Green** | **Green** | **Blue** | **Red** | **Yellow** |
| **Green** | **Blue** | **Red** | **Blue** | **Blue** | **Red** | **Green** | **Blue** | **Green** | **Blue** |
| **Yellow** | **Green** | **Red** | **Green** | **Yellow** | **Red** | **Blue** | **Red** | **Blue** | **Red** |
| **Red** | **Yellow** | **Red** | **Green** | **Green** | **Blue** | **Red** | **Yellow** | **Blue** | **Green** |

**Time: Second task ____________ sec Mistakes: Second task ___________**

**Investigator: _____________________**

**Stanford Sleepiness Scale**

( Hoddes et al., 1973 )

Please decide using the point-scale below what best represents how you are feeling and mark the corresponding number on the chart below.

Name: _________________________ Date: __________ ___________

| **Degree of sleepiness** | **Scale**  **Rating** |
| --- | --- |
| Feeling active, vital, alert, or wide awake | 1 |
| Functioning at high levels, but not fully alert | 2 |
| Awake, but relaxed; responsive but not fully alert | 3 |
| Somewhat foggy, let down | 4 |
| Foggy; losing interest in remaining awake; slowed down | 5 |
| Sleepy, woozy, fighting sleep; prefer to lie down | 6 |
| No longer fighting sleep, sleep onset soon; having dream-like thoughts | 7 |
| Asleep | X |

**Investigator : ______________________**

**STUDY FLOW CHARTS**

**Study title:** Normobaric hyperoxia for treatment of pneumocephalus after posterior fossa surgery in the

semisitting position: a prospective randomized controlled trial

**Patient’s selection, Informed consent, Stroop test**

**Surgery, Wound closure**

**ABG**

**< 2 hours**

**Cranial CT scan with image reconstruction**

**Intracranial air collection of 30 ml or more?**

**Yes No excluded**

**randomization**

**Group 1 Group 2**

**Ventilated with FiO2 100’% weaned off anaesthesia,**

**via the ETT extubation, ABG**

**3 hours**

**weaned off anaesthesia,**

**extubation, ABG**

**If necessary, further O2**

**via the ETT**

**primary endpoints:**

**cranial CT scan at 24 h after ventilation with FiO2 100’%**

**secondary endpoints:**

**Stanford Sleepiness Scale,**

**Stroop test**

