Normobaric oxygen has been suggested to be effective to treat pneumocephalus, since oxygen is able to replace nitrogen by increasing the diffusion gradient for nitrogen between the air collection and the surrounding tissue (Dexter & Reasoner, 1996). Using a mathematical model, proposed by Dexter and Reasoner in 1996, a FiO2 of 100% would be necessary to achieve significant air absorption within hours to days (Dexter & Reasoner, 1996). This model suggests that air would be resorbed faster if there is a greater gradient in the concentration of molecules between air and blood. The air resorption rate would be higher if there is less N2 dissolved in the blood of capillary arteries in the adjacent cerebral tissue. In 2008, Gore et al. demonstrated a significant increase of pneumocephalus resorption in 6 patients, who had normobaric hyperoxia at FiO2 68% over a non-rebreather mask for a period of 24 hours, resulting in a significant mean air volume reduction (Gore et al., 2008).

Considering that, we aimed to analyze the effect of administration of normobaric hyperoxia at FiO2 100% over an endotracheal tube (ETT) for 3 hours on pneumocephalus after posterior fossa surgery in the semisitting position. If higher air resorption rate were to be confirmed, a novel therapy approach will be established to reduce the postoperative morbidity.

Routine cranial CT scans with a secondary reconstruction of the volume of intracranial air will be performed immediately and 24 hours after surgery.

To assess the clinical state, patients will be requested to indicate their own level of sleepiness according to the Stanford Sleepiness Scale (Hoddes et al., 1973). Moreover, possible temporary frontal lobe dysfunction which correlates to pneumocephalus, will be assessed using the Stroop color-word interference test (Stroop JR, 1935; Eigelsreiter et al., 1986). The collected data and images will be compared and analysed.

1. **Study objectives**

The aim of this prospective randomized controlled trial is to prove, whether administration of normobaric hyperoxia at FiO2 100% might accelerate the resorption of postoperative supratentorial pneumocephalus after posterior fossa surgery in the semisitting position.

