A total of 44 patients aged 18 to 80 years will be randomized and evaluated after written informed consent are obtained. Patients randomized to the treatment group will be ventilated with normobaric hyperoxia at FiO2 100% via the endotracheal tube (ETT). Patients randomized to the control group will be weaned off from ventilation and will then be extubated.

The primary objective of this study consists of two co-primary endpoints. The first co-primary endpoint is the mean change of air volume between CT scan performed immediately and 24 hours after completion of surgery. The second co-primary endpoint is the air resorption rate, which is defined as the mean change of air volume divided by the time between the two CT scans.

Furthermore, the efficacy of normobaric hyperoxia at FiO2 of 100% on attention, as measured by the Stroop color-word interference tests, and on alertness, as noted on the Stanford Sleepiness Scale, will be compared and analyzed.

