**3. Randomization procedure**

Patients meeting the inclusion criteria will be randomized to treatment or control group after measurement of the air volume in cranial CT scan which will be performed immediately after completion of surgery. The randomization will be conducted independently from the patient recruitment at the Institute of Biostatistics. The Stroop color-word interference test will be performed one day before surgery and 24 hours after surgery by an Investigator, which is blinded to the treatment group.

1. **Patients selection**

We hypothesized that patients who will be treated with normobaric hyperoxia at FiO2 100% via endotracheal tube for 3 hours will show a significantly volume change and a higher resorption rate of postoperative pneumocephalus as compared to untreated patients. It is assumed, that there are no drop-outs in this trial.

Sample size is calculated based on the study by Gore et al (2008). In this study, 6 patients, who had normobaric hyperoxia at FiO2 68%, over a non-rebreather mask for a period of 24 hours, were compared to 7 patients who were breathing room air. Assuming a two-sided type I error of 5% and a power of 90%, for the mean change of pneumocephalus a total of 22 patients per study group (difference:16.6, common SD: 16.3) and for the mean air absorption rate (difference:1.37, common SD: 0.96) a total of 12 patients per study group are considered necessary. Subsequently, a total of 44 patients are necessary for recruitment. Moreover, it is assumed that the ANCOVA may enhance the statistic power.

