**4. Is this an investigation concerning effectiveness of drug therapy?**

No, there is no medication involved in this study.

1. **Patient safety and consideration of benefits**

This study should extend the understanding on the effect of normobaric hyperoxia at FiO2 100% on postoperative pneumocephalus. Patients in the treatment group will be ventilated with FiO2 100% over the endotracheal tube for a period of 3 hours. No adverse effects are expected after administration of normobaric hyperoxia in time duration of less than 48 hours on strictly selected patients (Jenkinson, 1993).

For the patients in the treatment group, acceleration of the air resorption of pneumocephalus might minimize the postoperative morbidity. Patients in the control group will be ventilated with room air until extubation according to standardized treatment. Thus, no additional complications or risks are expected. A specific benefit is also not expected.

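### The text times the follow-up CT from surgery, the flow chart from the FiO2 100% ventilation that only the treated arm receives; following the flow chart would favour treatment on the volume-change co-primary endpoint

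*Combined protocol and SAP*

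**What the plan says.** The documents time the endpoint CT in two ways.

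- **Text.** The background section says the routine CT scans "will be performed immediately and 24 hours after surgery". The Study objectives section defines the first co-primary endpoint as "the mean change of air volume between CT scan performed immediately and 24 hours after completion of surgery". Neither distinguishes the arms.
- **Flow chart.** Under the primary endpoints, the Study flow charts page has "cranial CT scan at 24 h after ventilation with FiO2" 100%. It gives no separate time for controls.

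The sequence of events is clear. The flow chart puts the first CT within 2 hours of wound closure. Patients are then "randomized to treatment or control group after measurement of the air volume in cranial CT scan". The section on patient safety states: "Patients in the treatment group will be ventilated with FiO2 100% over the endotracheal tube for a period of 3 hours". For the other arm, the Study objectives section states: "Patients randomized to the control group will be weaned off from ventilation and will then be extubated".

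The second co-primary endpoint is the volume change divided by the time between the two scans. Under Statistical consideration, both co-primary endpoints are analysed by ANCOVA with the respective baseline value. No term for the scan interval is listed, and no window is set for the second CT.

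**The concern.** The flow-chart origin depends on the arm. Controls have no FiO2 100% period, so for half the patients the label defines no time at all. For the treated half it places the second CT later than the text does, because all 3 h of ventilation fall after the baseline CT.

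The protocol's own background says intracranial air is resorbed spontaneously. Extra hours between scans therefore produce extra volume change even if oxygen does nothing. On a raw change adjusted only for baseline, that extra change would be counted as treatment effect. A scan taken at the wrong time cannot be repeated, and the flow chart is a page that staff may well schedule from.

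**Working it through.** **1. The plan's sample size.** Inputs from Patients selection: two-sided alpha 0.05, power 90%, difference 16.6 with SD 16.3 for the change, and difference 1.37 with SD 0.96 for the rate. The normal formula n = 2[(1.960 + 1.282) × SD / difference]² gives 20.3, so 21 per group, and 10.3, so 11 per group. The noncentral t gives 22 (power 91.0%) and 12 (power 91.6%), which are the plan's figures. They do not depend on the CT origin.

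**2. Interval between scans.** Inputs: first CT 0 to 2 h after surgery, and 3 h of ventilation assumed to start directly after that CT.

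| Reading | Treated | Control | Extra time, treated |
|---|---|---|---|
| Text origin in both arms | 22–24 h | 22–24 h | 0 h |
| Both arms timed from end of ventilation or extubation | about 27 h | about 24 h | about 3 h |
| Flow chart for treated, text for controls | 3 + 24 = 27 h | 22–24 h | 3–5 h |

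In the last row the treated interval is longer by 27/24 − 1 = 12.5% up to 27/22 − 1 = 23%.

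**3. Size of the bias.** The documents give no control resorption rate. They do say that asymptomatic air clears in 1 to 3 weeks, and entry requires at least 30 ml. I assume a baseline volume V of 30 to 60 ml (60 is my assumption), read the planned 16.6 as ml, and take no true oxygen effect.

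- *Linear, cleared in D days:* bias = (V/D) × h/24.
  - Smallest (30 ml, 21 days, 3 h): 1.43 × 3/24 = 0.18 ml.
  - Largest (60 ml, 7 days, 5 h): 8.57 × 5/24 = 1.79 ml.
- *First-order, assumed 95% cleared at D days:* k = −ln(0.05)/(24D), which is 0.01783 per h at 7 days and 0.00594 per h at 21 days. With t₀ the control interval, bias = V(e^(−k·t₀) − e^(−27k)).
  - Smallest (30 ml, 21 days, t₀ = 24): 0.46 ml.
  - Largest (60 ml, 7 days, t₀ = 22): 22.93 − 19.47 = 3.46 ml.
  - With only the 3 h gap, the largest is 22.93 − 20.89 = 2.04 ml.

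Against 16.6 the full range is 0.18/16.6 = 1% to 3.46/16.6 = 21%.

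**4. Effect on the type I error.** SE = 16.3 × √(2/22) = 4.91. The two-sided rejection rate comes from the noncentral t with 42 df at noncentrality bias/4.91.

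| Bias (ml) | Case | Rejection rate at nominal 5% |
|---|---|---|
| 0.18 | linear, smallest | 5.0% |
| 0.46 | first-order, smallest | 5.1% |
| 1.79 | linear, largest | 6.5% |
| 2.04 | first-order, largest with 3 h | 6.9% |
| 3.46 | first-order, largest with 5 h | 10.6% |

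**5. The rate endpoint.** Under linear resorption, dividing by time removes the gap. Under the 7-day first-order case with 60 ml, the treated rate is 22.93/27 = 0.849 ml/h. The control rate is 20.89/24 = 0.870 or 19.47/22 = 0.885, so the shift is 2.4% to 4.0% against treatment.

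**The case against.** The strongest reply is that the formal endpoint definition is in the Study objectives section, is common to both arms, and agrees with the background text. On that definition there is no extra time and no bias. The flow-chart line is a short label, and in the text available the chart has lost its layout, so one cannot see which arm or arms the CT box was drawn under. This stands as far as it goes: the bias is conditional. It does not remove the conflict, because both statements are current and nothing says which prevails.

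A reader might go further than the documents allow in three ways.

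- **That the 5 h gap is the expected one.** It needs treated patients timed by the flow chart, controls timed by the text, and a first CT almost 2 h after surgery. The documents never combine these. About 3 h is the more natural figure.
- **That the type I error could reach 17 to 38%.** That follows from spontaneous resorption of 40 ml per 24 h. Under linear clearance in one week it would need 40 × 7 = 280 ml of air at baseline, and nothing in the documents suggests such volumes.
- **That the Stroop test and the Stanford Sleepiness Scale share the conflict.** The Randomization procedure section gives the Stroop test a single origin: "The Stroop color-word interference test will be performed one day before surgery and 24 hours after surgery". The flow chart lists both tests without a time. The Stanford scale has no stated time anywhere, which is an omission and not a contradiction.

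**Conclusion.** The contradiction is established: one co-primary endpoint has two measurement times, and one of them is undefined for controls. Bias is not established. It arises only if treated patients are scanned by the flow chart, and it then favours treatment on the volume change.

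Its size is uncertain and probably modest: about 0.2 to 3.5 ml and a type I error of about 5 to 11%. The upper end needs one-week first-order clearance, 60 ml at baseline and the full 5 h gap together. These figures rest on the protocol's 1 to 3 weeks, the assumed volumes, and the planning SD. If ANCOVA reduces the residual SD, as the plan hopes, the same bias would inflate the error somewhat more.

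It might be inferred that the two co-primary endpoints are materially biased in opposite directions. That requires resorption that slows over time, which the documents do not specify, and even then the shift in the rate is only a few per cent. The rate endpoint largely removes the problem.

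The point still merits correction before scanning begins, because it concerns when a co-primary endpoint is measured.

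**What to change.** Reconcile the Study flow charts page with the background and Study objectives sections.

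1. Replace the flow-chart label with one time origin for the endpoint CT that applies to both arms. Either 24 h after surgery, as the text has it, or 24 h after the baseline CT would do. If the baseline CT is chosen, amend the background and endpoint wording to match.
2. State one window around that time, the same for both arms.
3. Report the actual interval between scans by arm. The scan times are already needed to compute the second co-primary endpoint.

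The cost is a wording change and one extra descriptive line in the report. No extra scans or patients are needed, and N = 44 is unchanged.
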